## Abstract

**Background:** As well as suffering a high burden of pneumococcal disease people living with HIV (PLHIV) may contribute to community transmission in sub-Saharan African (sSA) settings. Pneumococcal vaccination is not currently offered to PLHIV in sSA but may prevent disease and reduce transmission. More evidence of vaccine effectiveness against carriage in PLHIV is needed. An Experimental Human Pneumococcal Carriage model (EHPC) has been safely and acceptably used in healthy adults in Malawi to evaluate pneumococcal vaccines against carriage and to identify immune correlates of protection from carriage. This study will establish the same model in PLHIV and will be the first controlled human infection model (CHIM) in this key population.

**Methods:** Healthy participants with and without HIV will be inoculated intranasally with
*Streptococcus pneumoniae* serotype 6B. Sequential cohorts will be challenged with increasing doses to determine the optimal safe challenge dose to establish experimental carriage. Nasal fluid, nasal mucosal, and blood samples will be taken before inoculation and on days 2, 7, 14, and 21 following inoculation to measure pneumococcal carriage density and identify immune correlates of protection from carriage. The vast majority of natural pneumococcal carriage events in PLHIV do not result in invasive disease and no invasive disease is expected in this study. However, robust participant safety monitoring is designed to identify signs of invasive disease early should they develop, and to implement treatment immediately. Participants will complete a Likert-style questionnaire at study-end to establish acceptability.

**Interpretations:** We expect the EHPC model to be safely and acceptably implemented in PLHIV. The CHIM can then be used to accelerate pneumococcal vaccine evaluations in this population, and an evidence-based pneumococcal vaccination policy for PLHIV in sSA.

## Introduction

Controlled human infection models (CHIMs) involve the introduction of an infective agent to healthy volunteer participants in order to observe disease pathophysiology and evaluate vaccine efficacy. CHIMs in sub-Saharan Africa have demonstrated safety, feasibility, and acceptability, and have accelerated vaccine evaluations and development for pneumococcus and malaria
^
1,
2
^. Vaccine studies using CHIMs are cheaper and quicker than large clinical trials which rely on community exposure to pathogens in order to test vaccines, making them a promising tool in resource-limited settings or when disease incidence is very low
^
3
^. To date CHIMs have largely been implemented in young, healthy adults; the population with generally the lowest burden of infectious disease. It is important that CHIM studies be expanded to populations most affected by the disease, provided that this can be done safely. This will be the first study to implement a CHIM in a key at-risk population in sub-Saharan Africa, and for a disease that continues to represent a large burden of disease worldwide
^
4
^.

People living with HIV (PLHIV) are one of the most important populations to consider when addressing the burden of pneumococcal disease. They have a high burden of pneumococcal nasopharyngeal carriage, particularly if established on antiretroviral therapy (ART), with 26 to 52% of PLHIV in sub-Saharan Africa exhibiting pneumococcal carriage at any one time
^
5,
6
^. Pneumococcal nasopharyngeal carriage is a prerequisite for invasive pneumococcal disease such as pneumonia and septicaemia, and is required for onward transmission of the bacteria in the community
^
7
^. The high burden of pneumococcal carriage in PLHIV may form a reservoir for transmission in sub-Saharan Africa, and may be driving the ongoing pneumococcal carriage observed in vaccinated populations
^
8–
11
^. There is currently no pneumococcal vaccine policy for addressing pneumococcal carriage nor pneumococcal disease in PLHIV in sub-Saharan Africa. The 23-valent pneumococcal polysaccharide vaccine (PPV23) is associated with harm in PLHIV
^
12,
13
^, and while the 7-valent pneumococcal polysaccharide-conjugate vaccine (PCV7) is safe and effective for preventing vaccine-serotype disease
^
14
^, it has limited serotype-coverage
^
15
^. More evidence is needed to guide an evidence-based pneumococcal vaccination policy for PLHIV. The experimental human pneumococcal carriage (EHPC) model was established at the Malawi-Liverpool Wellcome Trust programme (MLW) in 2019 in order to accelerate vaccine evaluations and development. It has demonstrated acceptability to local stakeholders, and has successfully been used to evaluate vaccine efficacy for preventing pneumococcal carriage in healthy adults
^
15
^. This study will establish the EHPC in PLHIV with the translational aim of facilitating pneumococcal vaccine studies in this key population.

## Study protocol

### Study objectives

1.Establish the safety of experimental pneumococcal inoculation in PLHIV and the acceptability of the procedure to participants.2.Establish the rate and density of pneumococcal carriage in PLHIV compared to HIV negative adults after experimental pneumococcal inoculation.3.Identify the immune correlates of protection from pneumococcal carriage in PLHIV following experimental pneumococcal inoculation.

### Study hypotheses

PLHIV will exhibit higher carriage rate and density than HIV-negative controls following experimental pneumococcal inoculation.PLHIV will have perturbed mucosal and systemic immunity in response to experimental pneumococcal inoculation, compared to HIV-negative controls, which will predispose them to pneumococcal carriage.

### Study design

This study will use the same experimental design well-established at the Malawi-Liverpool Wellcome programme and at Liverpool School of Tropical Medicine
^
16,
17
^. Successive cohorts will be inoculated in both nostrils with an escalating, controlled concentration of live, penicillin-sensitive,
*Streptococcus pneumoniae* serotype 6B. Participants will be followed up for 21 days following inoculation during which sampling will occur at established time-points to establish pneumococcal carriage and cellular and humoral immune dynamics (
Figure 1). After 21 days, participants who exhibit pneumococcal carriage at any point during the study will commence a 3-day antibiotic course to clear the bacteria (participants may be advised by the clinical study team to commence antibiotics earlier if clinically indicated). A final health-check and exit interview will be conduction on day 25 to evaluate participant satisfaction with study participation.

**Figure 1. f1:**
[figure not shown]
Study design, sample collection and safety monitoring at different time points. Participants complete an information visit after which they can contact the study team if they wish to participate. Screening, informed written consent, and baseline sampling occurs within 7 days of inoculation. Inoculation is following by follow up visits on days 2, 7, 14, and 21 for nasal and blood sampling. On day 25 participants undergo a final health-check and exit questionnaire based on a Likert-scale. Nasal and blood sampling includes nasosorption to collect nasal fluid, nasal cells collected using nasal curettage, a nasal wash, a throat swab, saliva, and blood for serum, and peripheral blood mononuclear cells. Safety monitoring post-inoculation includes a residential stay for three nights, health-checks at each study visit, mobile phone contact with study team, an on-call study doctor 24/7, and a safety pack which is distributed to each participant (thermometer, antibiotics, battery pack for mobile recharging, safety information leaflet).

### Primary outcomes

Study objective 1:

Rate of solicited and unsolicited adverse events and serious adverse events recorded during scheduled and unscheduled study visitsParticipant satisfaction evaluated with a Likert-style questionnaire on day 25 post-inoculation

Study objective 2:

Pneumococcal carriage density of serotype 6B on days 2, 7, 14, and 21 post-inoculation in PLHIV and HIV-negative controls

Study objective 3:

Immunoglobulin G and A concentrations in nasal fluid or saliva respectively, and in blood plasma at baseline and on days 2, 7, 14, and 21 post-inoculationExploratory longitudinal analysis of immune cell frequencies and cellular activation at nasal mucosa and peripheral blood at baseline and at days 2, 7, 14, and 21 post-inoculation

### Study setting

Study visits will be conducted in MLW clinical research rooms in Blantyre, Malawi. Study samples will be processed in the adjacent MLW laboratory.

### Participant recruitment

Seventy-five HIV-negative adults and 75 PLHIV aged 25 to 45 years old.

### Study duration

Recruitment commenced June 2023. Recruitment will be completed within 18 months.

### Participant schedule

Participants will attend twice prior to inoculation in order to establish fully informed and voluntary consent, and to evaluate participant eligibility and safety to participate (
Figure 2).

**Figure 2. f2:**
[figure not shown]
Flowchart of schedule study visits. Participants attend 7 study visits over 25 to 32 days. Prior to attending for their first study visit, all participants must complete an information visit in which participants are provided all necessary information regarding the study and participation. Participant understanding is evaluated using a quiz prior to obtaining informed consent. Study visit 1 (informed consent and clinical screening) occurs within 7 days of study visit 2 (inoculation). Nasal and blood sampling occurs at every study visit except study visit 7. Study visit 7 consists of a health-check and an exit interview on participants’ experience of participation.

**
*Information visit:*
** Interested candidates will attend for an information visit where they will receive a description of the study and its objectives, and an outline of participation and its associated risks and benefits. This information will be given to potential participants verbally and in written form in English and/or Chichewa. Candidates will then be allowed a ‘cooling off’ period to consider whether they want to participate. Those who still wish to participate are invited to contact the study team and will be scheduled for a screening visit.

**
*Screening and consent visit (study visit 1):*
** Written consent will be obtained at this visit. A questionnaire will be conducted to ensure understanding of the study. Clinical screening will include a focused clinical history, a targeted clinical examination involving auscultation of the lung fields and heart sounds, blood sampling, a HIV antigen test if indicated, and a urinary pregnancy test if female. Blood samples will be obtained for full blood count, renal panel, and a HIV viral load and CD4 T cell count (if indicated) to evaluate participants’ fitness to participate in the study. Nasal cell and fluid samples and blood samples will be taken at this screening study visit to identify existing pneumococcal carriage, and to evaluate humoral and cellular immune markers. Participants naturally colonised with serotype 6B will not be eligible to continue in the study. Natural carriage with any other serotype can continue in the study. Should any previously unrecognised abnormality be identified during the screening visit, this will be explained to the individual, and appropriate investigations and follow-up will be arranged by the study team. Further participation will be determined at the discretion of the study doctor dependent on the nature of the abnormality detected. Eligible participants will be scheduled for their inoculation visit within 7 days of screening.

**
*Inoculation visit (study visit 2):*
** Participants will be inoculated with a microbiologically and genetically confirmed antibiotic-susceptible
*Streptococcus pneumoniae* serotype 6B strain BHN418. Inoculation will occur via a P200 micropipette containing 0.1 mL saline and a pre-specified dose of live pneumococcus. The inoculation dose will start at 20 000 colony-forming units per naris (cfu/naris). If a carriage rate of 50% is achieved in the first eight HIV-negative participants inoculated at this dose, all further participants will be inoculated at this dose. If the achieved carriage rate is below 50% then the dose will be escalated to 80 000 cfu/naris for the next eight HIV-negative participants. The dose may be further increased to 160 000 cfu/naris, then 320 000 cfu/naris, until the target carriage rate of 50% in HIV-negative participants is achieved. An adequate carriage rate is required in order to make statistical comparisons between participants, and in order to effectively evaluate vaccines in future studies using the model. Participants living with HIV will undergo the same dose escalation with close adverse event monitoring to establish safety in this population. The participant will be seated in a semi-recumbent position during inoculation. After inoculation, the participant will remain in this position for up to 15 mins and will be observed in the clinic room for 1 hour. Participants will receive a safety-pack including: i) A pocket-sized post-inoculation advice sheet with emergency contact details in English and Chichewa; ii) a digital thermometer and instruction on how to use it; iii) a course of amoxicillin with instructions of if and when to take them; and iv) a power-bank to ensure participants have access to a charged mobile phone to contact the study team if needed.

**
*Sampling visits (study visit 3-6):*
** Participants will attend for sampling visits on days 2, 7, 14, and 21 post-inoculation. At each sampling visit a member of the study team will complete a structured study visit template electronically which includes a wellness-check, a review of symptoms, a review of vital signs, and a review of intervening antibiotic-use. Samples taken during these visits are detailed below.

**
*Exit visit (study visit 7):*
** After the final sampling visit and completion of curative antibiotics (if indicated), participants will attend for an exit interview and final health check. The exit interview will be a structured electronic Likert-style questionnaire. The questions will cover five broad categories: Recruitment and consent; study procedures; study design and safety; study accommodation; and study participation.

If participants cannot attend on a particular post-inoculation study visit day then they can attend within 2 days of the scheduled visit.

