### Sample size calculation

The study will recruit 75 PLHIV and 75 HIV-negative controls aged 25–45 years old. The sample size is based on 50% carriage rate following inoculation in HIV-negative controls
^
17
^, and a 50% greater carriage rate amongst PLHIV based on community carriage point-prevalence
^
21
^. 132 participants (66 per group) will be required to achieve 80% power with p=0.05 so 150 participants will allow for some participant drop-out.

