^. Meanwhile, pneumococcal disease rate is reduced by a half to a third by ART, and rates of HIV-associated hospital admissions in Malawi have halved as ART is rolled out in the country
^
30,
31
^. Thus it can be inferred that the ratio of natural pneumococcal carriage to pneumococcal disease is very small and improves on ART. Experimental carriage is expected to be a similar benign event. Safety in this study is further enhanced by careful participant selection and by pneumococcal serotype selection. The exclusion criteria ensure that participants are well and stable on antiretroviral therapy. Risk of developing pneumococcal disease is strongly associated with CD4 T cell count
^
32
^, and all participants in this study will be immune-reconstituted and without additional risk factors for invasive pneumococcal disease. The pneumococcal serotype 6B used in the study has been selected for a lower carriage to disease ratio than other serotypes
^
33
^. Less than 2% of invasive pneumococcal isolates in Malawi are caused by serotype 6B and are largely seen in children if at all
^
34,
35
^.

Public and participant perception are a key consideration for CHIM studies in sub-Saharan Africa. The acceptability of the EHPC model to Malawian medical, research, and community stakeholders has been evaluated and provides a framework for this study to address ethical and safety considerations
^
18
^. For example, the study will use passive recruitment tactics to avoid potential participants feeling pressured by direct solicitation, as identified by stakeholder consultation. Reasons for participation in EHPC studies have been explored in detail in Malawi and provides guidance for avoiding undue solicitation during recruitment
^
36
^. Conducting a CHIM in PLHIV has been positively perceived by HIV stakeholders in Malawi during preliminary evaluations. The importance of giving PLHIV the opportunity to participate in research for the sake of equity and autonomy has been highlighted, while the need to balance risk to participants is recognised. Acceptability will be explored in a stand-alone study using qualitative methods running concurrently with this study.

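### As written, the acceptability outcome is collected only at the day-25 exit visit, so it describes completers and may overstate acceptability if people leave because of the procedures

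*Protocol article*

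**What the plan says.** Under Study objectives, the first objective is: "Establish the safety of experimental pneumococcal inoculation in PLHIV and the acceptability of the procedure to participants". Under Primary outcomes, the acceptability part of that objective has one measure, participant satisfaction on a Likert-style questionnaire at day 25. The Study design section and the legends to Figures 1 and 2 also place the exit interview or questionnaire at this last visit.

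The Participant schedule (Exit visit, study visit 7) fixes its position: "After the final sampling visit and completion of curative antibiotics (if indicated), participants will attend for an exit interview and final health check". The questionnaire covers recruitment and consent, procedures, design and safety, accommodation, and participation.

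The form for study visits 3 to 6 "includes a wellness-check, a review of symptoms, a review of vital signs, and a review of intervening antibiotic-use". All of these are health items. The only flexibility in timing is the visit window: "If participants cannot attend on a particular post-inoculation study visit day then they can attend within 2 days of the scheduled visit".

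Under Sample size calculation, "132 participants (66 per group) will be required to achieve 80% power with p=0.05", and "150 participants will allow for some participant drop-out". The Discussion adds: "Acceptability will be explored in a stand-alone study using qualitative methods running concurrently with this study".

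**The concern.** A measure taken once, after all sampling is finished, yields answers only from people who are still there. The questionnaire asks about the burdens that could plausibly make someone leave: intranasal inoculation, a residential stay, and repeated nasal curettage, nasal washes and venepuncture. If a participant leaves for one of these reasons, an unfavourable view of the procedure drops out of the outcome. The 2-day window helps a late attender but not someone who has withdrawn.

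The study presents itself as the first controlled human infection model in people living with HIV (PLHIV), and it is meant to open the way to vaccine challenge studies in them. The abstract expects the model to prove acceptable. A completers-only figure is weaker support for that than a figure that accounts for everyone inoculated. An analysis plan cannot repair this later, because it cannot recover answers that were not collected.

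**Working it through.** **1. The plan's own figure.** No figure is given for acceptability. The only computed figure is the sample size, and its margin is the one indication of how many participants might be lost.

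Inputs from Sample size calculation: control carriage 50%; PLHIV carriage 50% greater, read as relative, so 75%; 80% power; p = 0.05, taken as two-sided.

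- Mean proportion = (0.50 + 0.75)/2 = 0.625
- n = [1.960 × √(2 × 0.625 × 0.375) + 0.842 × √(0.50 × 0.50 + 0.75 × 0.25)]² / 0.25² = 57.7, so 58 per group without continuity correction
- With continuity correction: n = (57.7/4) × [1 + √(1 + 4/(57.7 × 0.25))]² = 65.4, so 66 per group and 132 in total

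The stated 132 is reproduced exactly. The margin is 150 − 132 = 18 participants, or 9 per group, and 18/150 = 12%.

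**2. What the margin could mean for acceptability.** Let N be the number inoculated, d the number who leave before the questionnaire, s the proportion satisfied among completers, and a the proportion satisfied among leavers.

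- Satisfaction over all inoculated = [s × (N − d) + a × d] / N
- Completer figure minus all-inoculated figure = (d/N) × (s − a)

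The values of s and a are assumptions. Setting N = 75 and d = 9 is also an assumption: it treats the whole margin as loss after inoculation.

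| s among 66 completers | a among 9 leavers | Over all 75 | Gap (points) |
|---|---|---|---|
| 90% | 0% | 59.4/75 = 79.2% | 10.8 |
| 90% | 50% | (59.4 + 4.5)/75 = 85.2% | 4.8 |
| 90% | 90% | 90.0% | 0 |
| 90% | 100% | (59.4 + 9)/75 = 91.2% | −1.2 |
| 95% | 0% | 62.7/75 = 83.6% | 11.4 |
| 80% | 0% | 52.8/75 = 70.4% | 9.6 |

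**3. Fewer leavers.** With 5 leavers among 150, none satisfied, and s = 90%, the gap is (5/150) × 0.90 = 3.0 points.

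The gap is thus the product of the share who leave and the difference in view between completers and leavers. The documents give neither quantity.

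**The case against.** The strongest objection is that this is a condensed article. It describes scheduled visits, and what happens at early withdrawal is commonly left to the full protocol. A reader might infer that people who leave are never asked and that the result is therefore biased upward. The documents support neither statement. No sentence says that leavers go unasked, and the list of items on the visit form is introduced as what it includes, so it need not be complete. Upward bias requires that people leave after inoculation, that they do so because of the procedures, and that they are not interviewed. This part of the objection stands, and it limits the point to a risk.

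The objection to the arithmetic also stands. The margin is set on participants recruited, for the carriage comparison. Consent is taken before screening results are known, and carriers of serotype 6B are excluded after that, so some losses may come before inoculation. Conversely, someone lost late may supply a carriage result and still miss day 25. The protocol also defines no percentage or threshold for acceptability, and it states no comparison of satisfaction between PLHIV and controls, so no bias in such a comparison can be claimed.

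Two further arguments carry less weight. Day 25 is a natural time for a questionnaire about the whole of participation, but that does not prevent its use at an earlier exit too. The concurrent qualitative study may add evidence, but it is described as stand-alone and its participants are not described. It can be assumed neither to reach those who withdraw nor to miss them, and it does not supply this primary outcome.

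What survives is that the outcome and its time point are stated. Taken as stated, they yield data from completers.

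**Conclusion.** The point holds as a risk and a cheap improvement, not as a demonstrated error. The acceptability outcome is fixed at one visit after all sampling, the article makes no provision for earlier leavers, and the sample size section expects drop-out.

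Under the illustrative assumptions (90% satisfied among completers, all 9 per group lost after inoculation), the completer figure would exceed the all-inoculated figure by about 5 points if half the leavers were satisfied and about 11 if none were. With few leavers it would be about 3 points or less. If people leave for reasons unrelated to the procedures, it would be near zero or slightly negative. These figures show what could happen under those assumptions and are not an estimate of bias in this study.

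**What to change.** In Primary outcomes and in the exit-visit text, add that the same questionnaire will be offered at withdrawal or last contact, by phone if needed, to anyone who leaves after inoculation, and that the reason for leaving will be recorded. State that the Likert results will be reported beside the number of withdrawals and their reasons, by group, over all inoculated participants.

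I would not score withdrawal for procedure-related reasons as a finding of not acceptable. That would turn a self-reported satisfaction measure into a composite that the protocol does not define. Reporting the two side by side is enough.

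The cost is small. The form is already electronic, every participant must have a mobile phone, and phone contact between visits is already planned under Safety monitoring. At most about 18 extra questionnaires would be needed if the whole margin were lost after inoculation. Some leavers will decline, and the reported picture may be less favourable. If the full protocol already provides for this, one sentence in the article settles the point.
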